## **6.5 Withdrawal of individual subjects**

Subjects can leave the study at any time for any reason if they wish to do so without any consequences. The investigator can decide to withdraw a subject from the study for medical or other reasons. Data collected prior to individual subject withdrawal will be used for data analysis, unless the patient requests otherwise.

## **6.6 Replacement of individual subjects after withdrawal**

We do not intend to replace individual subjects after withdrawal, as we anticipated a 25% of lost to follow-up. If the drop-out rate appears to exceed this estimation, we will reconsider.

## **6.7 Follow-up of subjects withdrawn from treatment**

If patients – for whatever reason – do not undergo the allocated treatment, this will be recorded as protocol deviation. Withdrawing from the randomized treatment is not a reason to terminate study participation, because follow up data of these patients are needed for intention-to-treat analyses. Therefore, patients will be invited for the study follow up measurements, and details of the treatment they received instead of the randomized procedure will be recorded. Subjects will be invited for all follow up measurements as described in this protocol, except those who explicitly withdraw informed consent.

## 6.8 Premature termination of the study

Any considerations to terminate this trial prematurely will be discussed with the research team, the sponsor, the subsidizing parties and the MEC-U.

## 6.9 Missing subjects

Subject can be missed during screening for study entry and subjects can refuse to participate in the study. Whether there are differences in baseline characteristics between the missing subjects and included subjects, data from the DHFA registration is collected. Of all consecutive patients treated with a hemiarthroplasty after femoral neck fracture admitted in one of the participating hospitals during the inclusion period, the following variables will be collected: age, gender, ASA, BMI, cognitive impairment and date of death.

## 7. SAFETY REPORTING

### 7.1 Temporary halt for reasons of subject safety

In accordance to section 10, subsection 4, of the WMO, the sponsor will suspend the study if there is sufficient ground that continuation of the study will jeopardise subject health or safety. The sponsor will notify the accredited METC without undue delay of a temporary halt including the reason for such an action. The study will be suspended pending a further positive decision by the accredited METC. The investigator will take care that all subjects are kept informed.

### 7.2 AEs and SAEs

#### 7.2.1 Adverse events (AEs)

Adverse events are defined as any undesirable experience occurring to a subject during the study, whether or not considered related to the surgical approach. All adverse events that are potentially related to the intervention and reported spontaneously by the subject or observed by the investigator or his staff will be recorded.

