### **6.2 Randomisation, blinding and treatment allocation**

Eligible patients admitted to the hospitals where both surgical techniques are practiced, are invited for participating in our RCT prior to the surgery. When patients agree to participate, written informed consent will be obtained and patients will be randomised between the PLA and the DLA. Randomisation will be stratified per center and per orthopaedic/trauma surgeon. Randomisation will be done in CASTOR EDC, a secured study and data management system with built-in randomisation (variable block method).

Surgeons, patients or outcome assessors cannot be blinded since the different surgical approaches are easily distinguishable (i.e. based on the location of the scar).

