#### 7.2.2 Serious adverse events (SAEs)

A serious adverse event is any untoward medical occurrence or effect that

- results in death;
- is life threatening (at the time of the event);

- requires hospitalisation or prolongation of existing inpatients' hospitalisation;
- results in persistent or significant disability or incapacity; or
- any other important medical event that did not result in any of the outcomes listed above due to medical or surgical intervention but could have been based upon appropriate judgement by the investigator.

An elective hospital admission will not be considered as a serious adverse event.

The investigator will report all SAEs related to the treatment to the sponsor without undue delay after obtaining knowledge of the events, except for the following SAEs; SAEs that are unrelated to the study intervention.

The sponsor will report the SAEs through the web portal *ToetsingOnline* to the accredited METC that approved the protocol, within 7 days of first knowledge for SAEs that result in death or are life threatening followed by a period of maximum of 8 days to complete the initial preliminary report. All other SAEs will be reported within a period of maximum 15 days after the sponsor has first knowledge of the serious adverse events.

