### **7.4 Data Safety Monitoring Board (DSMB) / Safety Committee**

Not applicable, as both study interventions are common procedures in the Netherlands.

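### Adverse event recording and SAE reporting are filtered by an unblinded relatedness judgement, and this is the only safety-reporting pathway the protocol defines

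*Protocol*

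**What the plan says.** Section 7.2.1 opens with a definition that ignores causality: "Adverse events are defined as any undesirable experience occurring to a subject during the study, whether or not considered related to the surgical approach". The next sentence sets the recording rule, and it is narrower: "All adverse events that are potentially related to the intervention and reported spontaneously by the subject", or seen by the investigator's team.

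Section 7.2.2 defines an SAE with no causal condition. For reporting it then says: "The investigator will report all SAEs related to the treatment to the sponsor without undue delay", "except for the following SAEs; SAEs that are unrelated to the study intervention". The sponsor forwards SAEs to the ethics committee from there. Section 7.3 follows only intervention-related SAEs to resolution or stability, and then says without qualification that SAEs must be reported until the study ends.

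On who judges and who oversees, section 6.2 says: "Surgeons, patients or outcome assessors cannot be blinded". Section 7.4 answers the DSMB question with: "Not applicable, as both study interventions are common procedures in the Netherlands". The annual report to the ethics committee (section 10.4) is to include serious adverse events.

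Outside section 7, section 6.1.2 lists number of falls, injuries from falling, re-interventions and complications as secondary outcomes. Section 6.4 collects complications and re-operations through the hip fracture audit registry and follow-up questionnaires. Section 6.9 collects date of death for all consecutive hemiarthroplasty patients at participating hospitals.

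**The concern.** An adverse event definition that disregards causality exists so that arms can be compared on everything that happened. A recording rule that then asks for a causal opinion removes that benefit.

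This matters more here than in most open trials. Section 1 states different expected harms by approach: dislocation after the posterolateral approach, and abductor weakness, poorer balance and falls after the direct lateral approach. A dislocation is easy to attribute to an approach. A readmission, a medical event or a death some months later in a frail patient usually cannot be attributed in the individual case, and only a comparison of all such events by arm would reveal a difference.

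At stake is safety oversight during the trial. Section 7.1 obliges the sponsor to suspend the study if there is sufficient ground to fear for subjects' safety. Under section 7.2.2 the sponsor is told only of SAEs that someone aware of the approach has called related.

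**Working it through.** The protocol gives no event rate or attribution rate, so there is no stated figure to reproduce. The check is mainly a comparison of sections.

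1. **Definition against recording (7.2.1).** The definition applies "whether or not considered related to the surgical approach". The recording rule requires potential relatedness, and also spontaneous report or observation by staff. An event can meet the definition and never be recorded.

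2. **Recording against reporting (7.2.1, 7.2.2).** The threshold tightens from potentially related, for recording an AE, to related, for reporting an SAE to the sponsor. Section 7.2.2 makes the investigator the reporter. Section 7.2.1 does not say who judges relatedness for AEs.

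3. **Reporting against follow-up (7.2.2, 7.3).** Section 7.2.2 exempts unrelated SAEs. The closing sentence of section 7.3 asks for SAEs to be reported to the end of the study and does not repeat the exemption. It may mean reportable SAEs only, but it does not say so.

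4. **Related to what?** The causal reference is the *surgical approach* in the AE definition, the *intervention* in the recording rule and in section 7.3, and both the *treatment* and the *study intervention* in section 7.2.2. The Summary gives the intervention as the posterolateral approach, with the direct lateral approach as comparator. Section 7.4 speaks of both approaches as study interventions. On the Summary's usage, an event caused by the direct lateral approach might not qualify.

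5. **Other capture.** Falls, fall injuries, complications and re-interventions are collected with no relatedness condition. Section 6.4 is not uniform about the source at 6 months: the text places the registry at baseline and 3 months with questionnaires at 6 months, while the table also lists the registry at 6 months. On either reading, complications and re-operations are collected to 6 months. Date of death is collected, but section 6.9 does so to compare missed with included patients.

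6. **Routing.** Nothing in sections 6.1.2, 6.4 or 6.9 sends those data to the sponsor or ethics committee for safety review. The SAE content of the annual report in section 10.4 has no stated source other than section 7.2.2. Complications are not defined, so medical SAEs and readmissions have no clearly stated unfiltered capture.

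7. **How the filter acts.** Let the true SAE rate be p in both arms, with probabilities a and b of being judged related. The ratio of reported rates is (p × a)/(p × b) = a/b. The values that follow are assumptions and do not come from the protocol:
   - a = b = 0.5: ratio 1.0
   - 0.6 against 0.5: 0.6/0.5 = 1.2
   - 0.7 against 0.4: 0.7/0.4 = 1.75
   - 0.8 against 0.3: 0.8/0.3 = 2.67

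The filter distorts the relative picture by arm only if attribution differs. Even with equal attribution, it withholds a fraction 1 − a of SAEs from the sponsor.

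**The case against.** The strongest reply is that the harms that matter most are already collected without a filter. Falls, fall injuries, complications and re-interventions are secondary outcomes in both arms, and section 8.2 compares dichotomous outcomes by chi-square and logistic regression. Section 8 plans no comparison of the adverse event log. This stands. A reader might infer that the hypothesised falls-related harm is lost, or that the arm comparison of outcomes is distorted. The protocol supports neither, because those outcomes do not pass through the relatedness judgement.

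Second, a broad definition followed by a narrower recording rule can be read as setting scope, and targeted recording is a defensible choice for two established procedures in a frail population. This stands in part: the definition does not promise that every event is recorded. It does not settle the changing causal reference or the unqualified sentence in section 7.3.

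Third, potential relatedness is a low bar, and by the protocol's own rationale dislocations and falls would meet it. That is fair for AE recording. It does not help with SAE reporting, where the bar is relatedness.

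Fourth, nothing shows that attribution does differ by arm. This also stands. Lack of blinding together with stated expectations makes it possible, but the protocol neither states it nor allows it to be estimated.

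**Conclusion.** The concern holds for safety reporting during the trial. The single defined pathway to the sponsor and ethics committee passes through an unblinded relatedness judgement that could differ by arm. There is no DSMB, and the causal reference is worded inconsistently. The sections need reconciling, because an SAE that is never recorded cannot be recovered in a later analysis plan.

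The concern does not extend to the planned comparison of falls, fall injuries, complications and re-interventions. What is left without clearly stated unfiltered capture is other SAEs, such as medical events and readmissions. Deaths are captured but not routed to oversight.

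No numerical size can be claimed. The ratios above rest on assumed attribution probabilities and would describe the SAE reports only. The conclusion assumes that no separate safety or monitoring document, not shown here, already requires all SAEs to be recorded. This is an inexpensive improvement and does not threaten the primary result.

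**What to change.** - Reconcile sections 7.2.1, 7.2.2 and 7.3 so that definition, recording, reporting and follow-up use one causal reference, and state that *the intervention* means either surgical approach.
- Record every SAE to 6 months in the electronic data capture system irrespective of relatedness, with relatedness as a separate field and the assessor named.
- Give the sponsor and ethics committee a periodic line listing by arm that includes unrelated SAEs and deaths. The annual report in section 10.4 is a natural place for it.
- Leave expedited reporting limited to related SAEs.

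The cost is some extra data entry at the existing 4-week, 3-month and 6-month contacts, plus preparation of the listing. The expedited reporting load does not change.

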#### 7.2.2 Serious adverse events (SAEs)

A serious adverse event is any untoward medical occurrence or effect that

- results in death;
- is life threatening (at the time of the event);

- requires hospitalisation or prolongation of existing inpatients' hospitalisation;
- results in persistent or significant disability or incapacity; or
- any other important medical event that did not result in any of the outcomes listed above due to medical or surgical intervention but could have been based upon appropriate judgement by the investigator.

An elective hospital admission will not be considered as a serious adverse event.

The investigator will report all SAEs related to the treatment to the sponsor without undue delay after obtaining knowledge of the events, except for the following SAEs; SAEs that are unrelated to the study intervention.

The sponsor will report the SAEs through the web portal *ToetsingOnline* to the accredited METC that approved the protocol, within 7 days of first knowledge for SAEs that result in death or are life threatening followed by a period of maximum of 8 days to complete the initial preliminary report. All other SAEs will be reported within a period of maximum 15 days after the sponsor has first knowledge of the serious adverse events.

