### **7.3 Follow-up of serious adverse events**

All SAEs related to the intervention will be followed until they have abated, or until a stable situation has been reached. Depending on the event, follow up may require additional tests or medical procedures as indicated, and/or referral to the general physician or a medical specialist.

SAEs need to be reported till end of study within the Netherlands, as defined in the protocol

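### The elective-admission exemption in Protocol 7.2.2 has no limit, so a planned admission for a complication of the study operation can fall outside expedited SAE reporting and 7.3 follow-up

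*Protocol*

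**What the plan says.** Section 7.2.2 of the Protocol defines an SAE by a list of criteria. One is an event that "requires hospitalisation or prolongation of existing inpatients' hospitalisation". Others are death, threat to life, persistent or significant disability, and "any other important medical event that did not result in any of the outcomes listed above due to medical or surgical intervention" but could have done so in the investigator's judgement. Directly after the list comes the exemption: "An elective hospital admission will not be considered as a serious adverse event". No condition is attached to it.

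The reporting duty follows: "The investigator will report all SAEs related to the treatment to the sponsor without undue delay after obtaining knowledge of the events". The same sentence excludes SAEs that are unrelated to the study intervention. The sponsor then reports to the METC within 7 days for fatal or life-threatening SAEs and within 15 days for the rest. Section 7.3 sets follow-up: "All SAEs related to the intervention will be followed until they have abated, or until a stable situation has been reached". Section 7.4 states that a DSMB does not apply.

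Outside the SAE route, section 7.2.1 provides for recording of "All adverse events that are potentially related to the intervention and reported spontaneously by the subject or observed by the investigator" or the study staff. Section 6.1.2 names re-interventions and surgical complications as secondary outcomes, and section 6.4 says how they are collected.

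**The concern.** An exemption of this kind normally serves to keep admissions that were going to happen anyway, such as long-planned surgery for another condition, from being counted as safety events. As written, it turns on whether the admission was elective, not on why it took place. An admission booked because of a complication of the study operation is elective too. It would otherwise meet the hospitalisation criterion, and it is the kind of event the reporting rules exist to catch.

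The matter has some weight here because the trial compares two surgical approaches that are expected to differ in their complications. Section 1 attributes a higher dislocation risk to the posterolateral approach and abductor insufficiency to the direct lateral approach. With no DSMB, reporting to the METC is the main external view of safety while the trial runs. Under the present sentence, whether an admission counts under the hospitalisation criterion can depend on whether it was booked or acute.

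**Working it through.** No arithmetic applies. The protocol gives no figure on this point, and the question is what the sentence does when read with the rules around it.

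**Step 1: what the two processes already exclude.** Expedited reporting in 7.2.2 covers treatment-related SAEs and expressly leaves out unrelated ones. Follow-up in 7.3 covers intervention-related SAEs. An unrelated elective admission is outside both, whatever the exemption says.

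**Step 2: what the exemption adds.** Elective admissions divide into three cases:

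| Elective admission | Reported and followed without the exemption? | With the exemption? | Effect |
|---|---|---|---|
| Unrelated to the study intervention | No, because of the relatedness limit | No | None |
| Related, and the complication meets another SAE criterion | Yes | Yes, through that other criterion | None |
| Related, and no other criterion is met | Yes, through hospitalisation | No | Removed |

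Only the third row changes. For reporting and follow-up, the sentence has no effect on the admissions it was presumably meant for. Its only effect is on related ones.

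**Step 3: whether the third row can occur.** It needs a complication that is not life threatening, did not lead to an acute admission or prolong the index stay, is not judged to cause persistent or significant disability, and is not judged an important medical event. A complication managed as an outpatient until a booked re-operation could fit. The important-medical-event criterion may catch it, but that depends on the investigator's judgement, whereas the hospitalisation criterion would have caught it without such judgement.

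**Step 4: what remains if the event is removed.**

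- Section 7.2.1: the complication is still recorded as a potentially related adverse event. That section sends nothing to the METC.
- Sections 6.1.2 and 6.4: complications and re-operations are collected through the DHFA at 3 months and by questionnaire at 6 months, including indications for re-intervention. This does not depend on SAE status, but it is scheduled data collection and not prompt reporting.
- Section 10.4: the METC receives a yearly summary that covers serious adverse events and other problems.
- Section 7.1: the sponsor's duty to suspend the study on safety grounds is not tied to SAE status.

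What can be lost is therefore the 7-day or 15-day report and the follow-up until the event settles. The data themselves are kept.

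**The case against.** The strongest reply is that the exempted item is the admission and not the complication behind it. An SAE is defined as an untoward occurrence or effect, so a dislocation, infection or loosening can be assessed on its own under the remaining criteria. An acute admission for dislocation is not exempt at all, and a revision after repeated dislocation presupposes earlier dislocations, each of which could have been assessed. This stands. It confines the problem to the third case in the working but does not remove it.

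A reader might go further and infer that a planned re-operation on the study hip can never be an SAE and is neither reported nor followed up. The documents do not support that. Another criterion may apply, potentially related adverse events are recorded, and re-operations and complications are collected as secondary outcomes whether booked or not. Nor does the protocol call planned re-operation the most approach-related serious harm; the harms it names by approach are dislocation and abductor insufficiency.

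A reader might also infer that the METC would have no other information, or that unblinded surgeons would book admissions differently by approach. The annual report contradicts the first. Nothing in the protocol shows the second, and the comparison of re-interventions rests on outcome data rather than SAE counts.

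Finally, it can be said that the intended meaning is obvious. That may be so, but sites apply the text as it is written, and the intended reading can be secured in one sentence.

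**Conclusion.** The point holds in a limited form. The exemption in 7.2.2 is unqualified, and because unrelated SAEs are already outside expedited reporting and 7.3 follow-up, its only added effect on those two processes is to let some treatment-related admissions drop out. This is a stated rule with an unintended effect, not a detail left for another document.

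The size cannot be calculated. The protocol gives neither a re-intervention rate nor the share that would be planned. A count built on assumed rates would at best be an upper bound, since it would treat every planned re-operation as related and as meeting no other criterion. The affected group is probably small. No efficacy estimate changes, and the between-arm comparison of re-interventions is unaffected.

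The conclusion assumes that sites apply the sentence literally and that some complications reach a booked admission without having met another criterion first. It is a cheap improvement to safety oversight and does not undermine the design.

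**What to change.** Replace the exemption in 7.2.2 with wording that turns on the reason for the admission, for example:

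*An elective admission planned before enrolment, or for a reason unrelated to the study intervention, does not count as an SAE. An admission for a complication of the study operation, booked or acute, is assessed under the hospitalisation criterion.*

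Using relatedness to the study intervention as the test, and not the operated hip, matches the rest of 7.2.2 and 7.3. There is no need to declare every re-intervention an SAE automatically; it is enough that the usual criterion applies.

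The cost is an edit to one short passage, notice to the sites, and a few more expedited reports. Relatedness must already be judged for reporting, so no new assessment is introduced. The primary analysis and the sample size do not change.
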